# A prospective, single-arm trial of fluorescent ureteroscopy-assisted thulium-holmium:YAG dual laser ablation for upper urinary tract cancer: Study protocol of the FLUAM trial

**DOI:** 10.1016/j.conctc.2022.100902

**Published:** 2022-03-02

**Keywords:** Upper urinary tract cancer, Transurethral surgery, 5-Aminolevulinic acid, Photodynamic diagnosis, UroVysion

## Abstract

**Background:**

Latest guidelines recommend kidney-sparing management as the primary treatment option for selected patients with upper urinary tract urothelial carcinoma (UTUC). One of the biggest issues of ureteroscopic laser ablation (ULA) is a high rate of surgical site recurrence, which is largely attributed to residual lesions at the initial ULA. Another clinical issue is a significant lack of non-invasive reliable detection tools of urinary recurrent tumors in this treatment setting.

**Methods:**

The FLUAM trial is a prospective, single-center, single-arm pilot trial to investigate the efficacy of 5-aminolevulinic acid-mediated photodynamic diagnosis (ALA-PDD)-assisted ULA for localized UTUC and the usefulness of the UroVysion® assay (multiprobe fluorescence in situ hybridization) as a monitoring test after the kidney-sparing treatment. After the screening and registration, a total of 20 patients with localized UTUC will undergo the initial ALA-PDD-assisted ULA followed by the second look ALA-PDD-assisted ureteroscopic examination. The primary endpoint is progression-free survival. Secondary endpoints include patient reported outcomes, diagnostic accuracy of UroVysion assay to detect tumor recurrence, adverse events, and safety of the intervention.

**Conclusion:**

The goal of this trial is to determine the potential benefit of ALA-PDD assistance in patients who undergo the ULA. The evidence of this novel technique is still limited. The results are expected to change the standard of care and lead to better management of localized UTUC.

**Trial registration:**

This clinical trial was prospectively registered with the Japan Registry of Clinical Trials on 23 June 2021. The reference number is jRCTs051210042, nara0023 (Certified Review Board of Nara Medical University).

## Introduction

1

Upper urinary tract urothelial carcinoma (UTUC) is relatively uncommon, accounting for only 5%–10% of all new cases of UC [1]. UTUC presents unique approaches for diagnosis, surgical treatment, and pre-/post-operative management. Radical nephroureterectomy (RNU) with removal of distal ureter (bladder cuff excision) is the gold standard for localized UTUC [[1], [2], [3]], but is associated with a significant loss of renal function [4,5]. Thus, kidney-sparing management involves alternatives that do not compromise oncological outcomes in well-selected patients [2,6,7]. The latest European Association of Urology guidelines on UTUC lists three recommendations as follows [2]:i)offer kidney-sparing management as primary treatment option to patients with low-risk tumors (strongly recommended),ii)offer kidney-sparing management (distal ureterectomy) to patients with high-risk tumors limited to the distal ureter (poorly recommended), andiii)offer kidney-sparing management to patients with solitary kidney and/or impaired renal function, providing that it will not compromise survival (strongly recommended).

Intraluminal ureteroscopic laser ablation (ULA) has provided acceptable oncological and functional outcomes, especially for patients with low-grade (LG)/low-volume tumors in the last two decades [[8], [9], [10], [11], [12]]. The recent advancement in visual technologies, flexible ureteroscopies, and laser energy equipment have made it more practical. Two reports demonstrated the safety and efficacy of thulium (Tm)-holmium (Ho): yttrium aluminum garnet (YAG) dual laser ablation [8,9]. The combination of Tm:YAG laser with continuous wave and Ho:YAG laser with long pulse mode enables efficient tumor coagulation, vaporization, and resection under comfortable visual control. One of the biggest concerns of ULA is high rate of surgical site recurrence, reportedly ranging from 30.7% to 90.5% [[9], [10], [11], [12], [13]], which is largely attributed to residual lesions at the initial ULA. Previous reports demonstrated the advantage of oral 5-aminolevulinic acid-mediated photodynamic diagnosis (ALA-PDD) using fluorescent ureteroscopy to detect invisible lesions, with conventional white light endoscopy [[14], [15], [16]]. Our primary interest in this clinical trial was whether the use of PDD technology provides decreased surgical site recurrence and subsequent progression, through complete resection of UTUC.

The patients should be followed up closely in kidney-sparing management. Ureteroscopy with or without biopsy, cystoscopy, urinary cytology, and chest/abdominal/pelvic computed tomography (CT) or magnetic resonance imaging (MRI) are performed at regular intervals for surveillance [2,8]. Unfortunately, there is a significant lack of non-invasive reliable detection tools of urinary recurrent tumors in this treatment setting. Previous studies suggested that the UroVysion® test was a useful tool for the diagnosis not only of primary UTUC but recurrent UTUC after kidney-sparing surgery [17,18].

This prospective, single-center, single-arm pilot trial will investigate the efficacy and safety of ALA-PDD-assisted ULA for localized UTUC and the feasibility of UroVysion test combined with conventional urinary cytology as a detection marker of recurrent UTUC after the kidney-sparing surgery.

## Protocol digest of the FLUAM trial

2

### Study type and ethical issues

2.1

This clinical trial is a prospective, single-center, single-arm trial for patients with localized UTUC, which is ongoing at Nara Medical University Hospital. This trial complied with the Declaration of Helsinki regarding investigation in humans. Its ethical clearance and the final study protocol (version 1.0 on June 21st, 2021), including the subject information, informed consent forms, and associated documents, were approved by the Certified Review Board of Nara Medical University (institution ID: CRB5200002). Informed consent and written consent forms of patients are mandatory before study participation. This clinical trial was prospectively registered with the Japan Registry of Clinical Trials on June 28th, 2021 (the reference number: jRCTs051210042). The URL of trial registry record is found in https://jrct.niph.go.jp/latest-detail/jRCTs051210042.

### Inclusion criteria

2.2

The flow chart, patient enrolment, endpoints of the FLUAM trial are depicted in Fig. 1. The trial design and protocol adhere to the Recommendations for Interventional Trials (SPIRIT) criteria [19]. The completed SPIRIT checklist can be found in Supplementary data. Investigators and patients will be aware of the intervention of oral administration of ALA. Patients will undergo a general work-up and radiographical examinations, including CT, CT-urography (CT-U) or MRI, cystoscopy, and urine cytology. Diagnostic ureteroscopy with biopsy ± upper urinary tract catheterization or irrigation cytology are performed to evaluate the tumor grade, tumor location, architecture, and feasibility of the ULA. Tumors are staged and graded according to the eighth edition of the American Joint Committee on Cancer (AJCC) TNM classification [20], by an experienced uropathologist ([name]). Prior to enrolment in this trial, patients must meet all of the following inclusion criteria:(i)Patients with clinical Ta–1N0M0 localized UTUC desire kidney-preservation therapy and meet any of the following A to E.A.Tumor develops in patients with solitary kidney or tumor develops bilaterally.B.Patients with chronic kidney disease are expected to avoid renal replacement therapy in the future by kidney-preservation therapy.C.Due to poor performance status, it is clinically judged that total RNU is not indicated.D.Patients have a single tumor with a major axis of 10 mm or less and have a healthy kidney on the contralateral side.E.Patients desire kidney-preservation therapy, although they are recommended RNU.(ii)Age, 20 years or older (regardless of gender)(iii)The pathological diagnosis is confirmed by ureteroscopic biopsy.(iv)The name and disease status have been informed to the patient, and he/she must be given an explanation when participating in this study. The written consent at his/her must be obtained with sufficient understanding.(v)Bone marrow function and organ function (excluding renal function) are sufficient by the following laboratory findings within 60 days:A.Hemoglobin ≥9.0 g/dL (no transfusion within 4 weeks)B.White blood cell count, the lower limit to 12,000/mm^3^C.Neutrophil count ≥2,000/mm^3^D.Platelet count ≥100,000/mm^3^E.Total bilirubin ≤2 × the upper limit of normalF.Aspartate aminotransferase (AST) ≤ 2 × the upper limit of normalG.Alanine aminotransferase (ALT) ≤ 2 × the upper limit of normal

**Fig. 1 fig1:**
[figure not shown]
**The flow chart, patient enrolment, endpoints of the FLUAM trial.** Patients must meet all the inclusion criteria to be eligible for this trial.

### Exclusion criteria

2.3

Prior to enrolment in this trial, patients must not meet any of the following exclusion criteria:(i)Patients with a history of allergic reaction to ALA.(ii)Pregnant women, lactating women, and patients who may be pregnant.(iii)Patients with liver dysfunction and inflammatory disease.(iv)Patients with porphyria or patients with a history of allergic reaction to porphyrin-related substances.(v)Patients taking concomitantly prohibited drugs and foods, which are known to cause photosensitivity (skin reaction): Tetracycline antibiotics, sulfonamides, new quinolone antibacterial agents, hypericin (Hypericum erectum extract), etc., Hypericum erectum (St. Jones Wort)(vi)Cases in which patients cannot give consent or take the medicine on their own initiative.(vii)Deemed inappropriate for enrolment as per the judgment of the physician.

### Preoperative procedure and surgical device

2.4

Approximately 3 h (range, 2–4 h) prior to ULA, patients received by mouth the water-dissolved ALA hydrochloride solution (SBI Pharmaceuticals, Tokyo, Japan) at a dose of 20 mg/kg body, which is the same dose as the current clinical practice for non-muscle invasive bladder cancer in Japan [21].

The ULA is performed under general or spinal anesthesia in the lithotomy position. Tumor visualization and PDD assistance was carried out using the Storz D-LIGHT System (KARL STORZ GmbH & Co. KG; Tuttlingen, Germany) and the Storz Professional Image Enhancement System (IMAGE1S™, KARL STORZ). Rigid 7-Fr Ureto-Renoscopes, flexible Ureto-Fiberscopes Flex-X^2^, and an eyepiece filter specific for detection of protoporphyrin IX (KARL STORZ) were used. We can switch imaging modes of white light and blue light frequently during the operation to set the resection margin and detect the residual lesion. A UROMAT E.A.S.I. (KARL STORZ) is used to keep appropriate pressure levels to obtain an adequate irrigation flow during the ULA, especially for renal pelvic tumors. A Revolix 120 Tm:YAG laser system and Sphinx jr. Ho:YAG laser system (LISA Laser Products OHG, Katlenburg-Lindau, Germany) are used for tumor laser ablation. For both laser systems, 272-mm or 550-mm laser fibers are used depending on the tumor location and the use of flexible ureteroscope or rigid ureteroscope.

### Surgical procedure of ALA-PDD-ULA

2.5

Resection and ablation of all the visible tumors is performed according to the surgical method as previously described [8]. A ureteral access sheath (10/12-Fr to 12/14-Fr) is placed depending on the ureteral condition, and a flexible ureteroscope is used for proximal ureteral tumors or renal pelvic tumors, while a rigid ureteroscope is used for distal or middle ureteral tumors. Tumors are first observed with caution under white light mode and PDD mode to determine resection margin. Then, vaporization and coagulation by Tm: YAG laser are performed. Ablation and resection by Ho:YAG laser can be added on a case-by-case basis after the tumor becomes ischemic. Large tumor fragments are retrieved using a stone extraction basket. Lastly, observation under the PDD mode is performed to detect residual lesion and, when present, the tumors are additionally ablated with the Tm:YAG and Ho:YAG lasers until all PDD-positive tumors are eradicated. A representative case treated with ALA-PDD-ULA is shown in Fig. 2. A 6-Fr double J-stent ureteral stent and a urethral catheter were inserted at the end of surgery. All patients were instructed to avoid exposure to sunlight or bright indoor light for up to 48 h after oral administration of ALA.

### Follow-up schedule and data collection

2.6

Patient data will be collected before and after the surgery; 1, 3, 6, 9, 12, 15, 18, 21, 24, and 27 months after the initial ALA-PDD-ULA; and at the end of the trial (Fig. 3). To improve monitoring adherence, the clinician will take time to explain the need for post-operative surveillance examination, including second-look URS, and encourage the participants to undergo routine cystoscopy, urine cytology, and CT/CT-U/MRI. The assessment includes patient-reported outcomes, such as the SF-8™, EORTC QLQ-C30, FACT-BL, International Prostate Symptom Score (IPSS), and overactive bladder symptom score (OABSS). The postoperative observational evaluation such as PROs can be discontinued upon participant request. The data will be documented in specific Case Report Forms for complete blood count, serum chemistry, cystoscopy, urine cytology, CT/CT-U/MRI, genitourinary adverse events (AEs), and other possible AEs using the Common Toxicity Criteria for Adverse Events (CTCAE v 5.0). When recurrence is suspected in imaging examinations, ALA-PDD-ureteroscopy is considered and, if recurrent tumor is present, ALA-PDD-ULA is additionally performed. AEs strongly related to the intervention of ALA-PDD-ULA are listed as follows: “Intraoperative urinary injury,” “Urinary tract infection,” “Fever,” “Renal hemorrhage,” “Hematuria,” “Creatinine increased”, “Urinary frequency”, “Photosensitivity”, “Hepatobiliary disorders”, “Urinary tract pain”, “Urinary urgency”, and “Dysuria”. Any other potential AEs are recorded and grouped into ‘related AEs’ or ‘unrelated AEs.’ When serious AEs occur, investigators report to the Safety Monitoring Committee.

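### As worded, twelve adverse event terms are attributed to ALA-PDD-ULA by name and only the remaining events get a related/unrelated judgement, so background events under non-specific terms would be labelled intervention-related

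*Protocol article*

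**What the plan says.** Protocol article, section 2.6 (Follow-up schedule and data collection), introduces a list of twelve terms with "AEs strongly related to the intervention of ALA-PDD-ULA are listed as follows". The terms are intraoperative urinary injury, urinary tract infection, fever, renal hemorrhage, hematuria, creatinine increased, urinary frequency, photosensitivity, hepatobiliary disorders, urinary tract pain, urinary urgency and dysuria. The next sentence reads: "Any other potential AEs are recorded and grouped into ‘related AEs’ or ‘unrelated AEs".

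The same section collects data before and after surgery and then at "1, 3, 6, 9, 12, 15, 18, 21, 24, and 27 months after the initial ALA-PDD-ULA; and at the end of the trial".

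The Abstract gives AEs an endpoint role: "Secondary endpoints include patient reported outcomes, diagnostic accuracy of UroVysion assay to detect tumor recurrence, adverse events, and safety of the intervention". Section 2.10 assigns the secondary endpoints other than survival outcomes to the per-protocol set and gives no further rule for counting AEs.

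**The concern.** The two sentences in section 2.6 together work as an attribution rule. The first assigns causality by term. The second describes the related/unrelated step and, through the word other, confines it to terms not on the list. A listed event therefore gets its label from its name, whatever its timing, the patient's baseline or a competing explanation.

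For several of the terms this does not suit the population or the length of follow-up. The disease, the comorbidity that made the patient eligible, or ordinary background illness can produce the same event. With one arm, no concurrent rate shows how much of the observed frequency is background. Event-level judgement is then the main means of separating harm of the intervention from the rest. If that judgement is skipped for the commonest urological terms, the related-AE rates for those terms are biased upward. Some tumour recurrence, which is treatment failure, could also be recorded as treatment toxicity.

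**Working it through.** There is no stated figure to reproduce. The check is a reading of the text, followed by simple arithmetic on size.

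**1. Scope of the rule.** Twelve terms are listed. The related/unrelated grouping is described once, for AEs other than these. The text ties no onset window to the listed terms, and visits run to 27 months and the end of the trial.

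**2. Which terms are exposed.** Set against the rest of the article:

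- *Creatinine increased.* Section 2.2 admits patients with a solitary kidney or bilateral tumours, and CKD is a route of entry: "Patients with chronic kidney disease are expected to avoid renal replacement therapy in the future by kidney-preservation therapy". Renal function is left out of the laboratory entry limits: "Bone marrow function and organ function (excluding renal function) are sufficient". A rise unrelated to the procedure is therefore plausible.
- *Hematuria.* The Introduction reports a "high rate of surgical site recurrence, reportedly ranging from 30.7% to 90.5" percent after laser ablation, and bleeding can be a sign of recurrent tumour.
- *Infection, fever, pain, frequency, urgency, dysuria.* These can occur long after any procedure or be present at entry.
- *Not exposed.* Intraoperative injury and photosensitivity are naturally tied to the procedure or the agent. Stent and catheter effects also belong to the intervention, because section 2.5 makes both part of the operation: "A 6-Fr double J-stent ureteral stent and a urethral catheter were inserted at the end of surgery".

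**3. Size per mislabelled patient.**

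- All 20 patients: 1/20 = 5.0 percentage points.
- Per-protocol set: section 2.7 allows for 20–30% ineligible. Assuming all of these leave the set, 20 × 0.8 = 16 or 20 × 0.7 = 14 patients remain. Then 1/16 = 6.25 and 1/14 = 7.1 points.

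**4. How many patients could be involved.** The document gives no background rate. As an assumption only, let b be the share of patients who have a listed event from background causes alone. The expected number among 20 is 20 × b, and the chance of at least one is 1 − (1 − b)^20.

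| assumed b | expected patients | P(at least one) |
|---|---|---|
| 10% | 2 | 88% |
| 20% | 4 | 99% |
| 30% | 6 | over 99.9% |
| 50% | 10 | over 99.9% |

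The table shows only that at least one such event would be likely even at a modest background rate. It does not estimate the bias in this trial.

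**The case against.** The strongest reply is that the list may simply mean anticipated AEs. The article condenses a full protocol, where per-event causality, reporting windows and form fields would normally sit. That is fair as far as it goes, and silence on those details is not a fault here. But the article is not silent. It describes a causality step and restricts it to unlisted events, and it calls the listed ones strongly related rather than expected. If causality is in fact judged for every event, the sentence misdescribes the plan and still needs correcting.

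Other points on that side stand:

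- A reader might infer that all listed events, stent effects included, will be counted as harm of ALA-PDD-ULA. No section says so, section 2.10 has no such counting rule, and stent and catheter effects are properly part of the intervention.
- A reader might infer that the list lets events slip past the safety committee. Section 2.6 sends serious AEs there with no relatedness condition, so nothing is bypassed.
- A late event can be genuinely related, because a second-look ureteroscopy is planned and ALA-PDD-ULA may be repeated for recurrence. This is a reason to date onset from the most recent procedure, not from the first.
- Baseline creatinine, International Prostate Symptom Score (IPSS) and overactive bladder symptom score (OABSS) are collected. Much of the background can therefore be recovered, and it would be too strong to say the trial cannot answer the safety question.
- Over-attribution errs on the cautious side for safety. It is still a bias, and it blurs toxicity with recurrence.

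**Conclusion.** The point holds as a matter of wording that fixes attribution badly. Taken literally, section 2.6 labels background events under non-specific terms as intervention-related, mainly creatinine increased, hematuria, and late or pre-existing infection, fever and urinary symptoms. The single-arm design offers no control rate to correct this.

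The consequence is confined to the secondary safety endpoint; the progression-free survival test and the sample size are untouched. One mislabelled patient shifts a rate by 5 points on 20 patients, or by about 6 to 7 points on 14 to 16. The latter range assumes that the ineligible share is removed from the per-protocol set. How many patients would be mislabelled cannot be derived from the document. The conclusion also assumes that the sentence is applied as written; a full protocol that already requires per-event causality would reduce the matter to a correction of the text.

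**What to change.** Reword section 2.6 so that:

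1. the twelve terms are called anticipated AEs, to be actively recorded at each visit;
2. the related/unrelated judgement applies to every AE, listed or not;
3. each AE carries its onset relative to the most recent procedure and the patient's baseline status for that term, using the creatinine, IPSS and OABSS values already collected;
4. the report shows related AEs and all AEs regardless of cause.

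A finer division of cause into drug, laser, stent and disease is optional and not needed to resolve this point.

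The cost is slightly more case report form work, with no added visits. Follow-up runs to June 2026, so the change is best made while events are still being recorded; any listed events already captured without a judgement would need one retrospectively. The downside is that an investigator's causality judgement in an open trial is subjective, which the all-cause report offsets.

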**Fig. 3 fig3:**
[figure not shown]
Intervention and assessment schedule of the FLUAM trial. Follow-up visits and data collection should occur approximately 1, 3, 6, 9, 12, 15, 18, 21, 24, and 27 months from the initial surgery. Patients will complete a set of questionnaires at every visit, and follow-up information may be collected via medical charts. The Case Report Form will include information regarding past history, concomitant medications, and any medications taken after the treatment. Chest–abdomen–pelvis computed tomography (CT) and/or magnetic resonance imaging (MRI) should be performed for TNM classification. X, mandatory; (X), optional, ALA-PDD-ULA after 6 months is performed when the radiographic examination suspect tumor recurrence in the upper urinary tract. *hemoglobin, hematocrit, white blood cell count and fractions, platelet count; **aspartate transaminase (AST), alanine transaminase (ALT), γ-glutamyl transpeptidase (γ-GTP), total bilirubin, alkaline phosphatase (ALP), lactate dehydrogenase (LDH), total protein, albumin, serum creatinine, blood urea nitrogen, uric acid, total cholesterol, triglyceride, C-reactive protein (CRP), sodium, potassium, chloride; ***Urine dipstick test (specific gravity, pH, protein, glucose, bilirubin, urobilinogen, ketone body, and occult blood) and urine sediment test; †according to the Common Toxicity Criteria for Adverse Events (CTCAE v 5.0) translated into Japanese; †† questionnaires SF-8™, EORTC QLQ-C30, and FACT-BL. Abbreviations: BW, body weight; BT, body temperature; BP, blood pressure; ALA, 5-aminolevulinic acid; PDD, photodynamic diagnosis; ULA, ureteroscopy laser ablation; QOL, quality of life; IPSS, International Prostate Symptom Score; OABSS, overactive bladder symptom score.

To protect the patient's personal information, unique identification codes (FLUAM IDs) will be assigned to all patients. All the data will be protected in password-accessible electronic data files on secure servers before, during, and after the trial, and only investigators will be able to access the files. All data and documents will be deleted and discarded five years after the trial ends, unless the data are being used for another study.

